Cumulative live-birth rate within three years from first treatment (surgery or ART treatment).

Definition of primary outcome measure

CLBR is defined as any live births from first treatment until end of follow up (three years from first ART treatment or surgery or drop out from the study, whichever comes first).

Primary outcome will be calculated considering also the following pre-specified subgroups: study center,  type of ART-treatment (IVF or ICSI), age (< and > 35 years), ovarian reserve ( anti-mullerian hormone (AMH) <0.5ng/L, 0.5-3.5 ng/L and AMH >3.5ng/L ) (35) adnexal surgery (yes/no), surgery on deep endometriosis anterior compartment (yes/no) or deep endometriosis posterior compartment (yes/no) (defined by Classification of surgery, “Klassifikation av vårdåtgärder” (KVÅ codes), see appendix).

SECONDARY OUTCOME MEASURE

- Cumulative Pregnancy Rate (CPR)
- Time to pregnancy and live birth
- Spontaneous Pregnancy Rate
- Miscarriage rate and/or extrauterine pregnancies
- Reproductive outcomes per IVF cycle
- Rate of recurrent implantation failure (RIF), (20) evaluated at the end of the study period
- Infections after oocyte pick-up
- Quality of life and pain
- Peri- and two months postoperative complications classified by Clavien-Dindo and Classic systems
- Health care costs
- Obstetrical outcomes and complications
- P-progesterone levels on day of embryo transfer at first HRT frozen-thawed artificial embryo transfer cycle

Definition of secondary outcome measures

Cumulative Pregnancy Rate (CPR) is defined as all pregnancies confirmed with ultrasound, from first treatment (surgery or ART) until three years of follow up.

Time to pregnancy is defined as time from first treatment (surgery or ART) to first pregnancy confirmed with ultrasound. Time to live birth defined as time from first treatment (surgery or ART) to first livebirth.

Spontaneous pregnancy rate is defined as any spontaneous pregnancy occurring between first treatment and end of follow-up.

Miscarriage rate defined as frequency and proportion of spontaneous loss of any clinical and biochemical pregnancy before week 22 and/or extrauterine pregnancy defined as a pregnancy not located in the uterine cavity, occurring between first treatment and end of follow-up.

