The study will end when all patients enrolled in trial have been followed for 3 years after first treatment, withdrawn consent, or are lost to follow-up. Data from study participants that are lost to follow will be included in the final analysis. The trial steering committee may end enrolment at any time if it is deemed that this is in the best interest of the patients.

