# LONG-TERM FOLLOW-UP

There will be an opportunity for inclusion in a long-term follow-up, where participants from both the randomized controlled study and the cohort study will be eligible if they consent. In the long-term follow-up, conducted 10 years post-inclusion, we will utilize the unique Swedish personal identification number and gather data after study conclusion on infertility treatments from the National Register of ART in Sweden (Q-IVF) live births from the Swedish Medical Birth Register (MFR) and The National Pregnancy Register and number of recurrent endometriosis surgeries from Gynop. For details about variables collected from each register see appendix.

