# STATISTICAL CONSIDERATIONS

The primary exposure is the randomized allocation (surgery prior to ART vs ART alone). All analyses will follow the intention-to-treat (ITT) principle, meaning participants are analyzed according to their randomized group regardless of adherence. Per-protocol and as-treated analyses will be conducted as sensitivity analyses to assess robustness. An interim analysis at the halfway point is planned to monitor potential adverse effects and ensure the safety of the interventions.

No formal adjustment for multiplicity will be made; the primary endpoint will be tested at a two-sided α=0.05, while secondary endpoints are considered supportive and exploratory. Sensitivity analyses will address protocol deviations, handling of missing data, and robustness to alternative modelling approaches.

DATA ANALYSES

Baseline demographic and patient’s characteristics will be summarized by treatment group. Continuous variables will be described with mean, standard deviation, median, interquartile range, minimum and maximum, and categorical variables with counts and percentages.

Primary endpoint

The primary endpoint of the study is the Cumulative Live Birth Rate (CLBR), defined as the proportion of participants achieving at least one live birth within three years following the initiation of treatment.

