**Additional analysis**

– Exploratory subgroup analyses will not be adjusted for multiplicity.

– Safety outcomes will be summarized descriptively by treatment group (frequency, severity, relation to treatment).
– All available data will be used, including outliers.
– Missing outcome data will be handled under the missing-at-random assumption via maximum likelihood in mixed models; for regression models requiring complete covariates, complete-case analysis will be applied.

Covariates

Primary and secondary outcomes will be adjusted for prespecified covariates (age, BMI, AMH, ART type, center), chosen based on clinical relevance and prior evidence.

POWER CALCULATION AND SAMPLE SIZE

The sample size calculation was based on a two-sample comparison of proportions with a two-sided α=0.05 and 80% power. Based on observational data (18, 19), the cumulative live birth rate (CLBR) after three IVF cycles was assumed to be 55% in the ART-only group and 71% in the surgery+ART group (relative risk ≈1.29). This yields a required sample size of 142 participants per arm (284 total). Allowing for 20% attrition, the planned total sample size is 350 participants.

The necessary sample size for this study is estimated to 323 patients to accommodate a statistical analysis method. This estimation uses the 'pwr' package in R, specifically employing the power.prop.test method, which is designed to compare two proportions. This method is more aligned with contemporary statistical practices and provides a clear, transparent methodology for determining the required sample size based on expected success rates.

This means inclusion of 29 patients from/each center/year and 15 surgeries/year. In a Swedish study published in 2022 the prevalence of endometriosis in patients referred for ART-treatment was 21.8% and 17.2% of women had DE (14). In 2021 almost 10 500 IVF cycles were performed in Sweden, while more than 5 500 of those were first-time IVF/ICSI with autologous gametes ((46) Figure 22).

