# DATA MANAGEMENT AND QUALITY CONTROL

DATA COLLECTION

Data for the randomized controlled study will be collected from medical records. In case of missing information patients will be contacted by phone or through secure electronic data platforms (e.g “Alltid Öppet”) for additional information. Data from ultrasound examination, surgeries and IVF treatments will be documented either directly into the eCRF or in paper forms. The results from the blood samples (AMH and P-Progesteron) will be collected from the medical records. No blood samples will be stored for future use in this study.

For the sub-studies data will be collected from the following sources:

- Quality of Life: Questionnaires are sent from the eCRF RedCap and patients´ answers will be electronically collected directly into the eCRF.
- Health Economy: Cost per patient will be collected from each site’s economical system.
- Adenomyosis: Medical records and Data forms or paper forms as described above.
- P-Progesterone: Medical records and Data forms or paper forms as described above.
- Obstetrical Outcomes: Either from medical records or the MFR at the end of the study. If data is missing, patients can be contacted by phone or through secure electronic data platforms (e.g “Alltid Öppet”) for additional information.
- Prospective cohort study: Data will be collected in the same way as in the RCT.
- Long-term follow up: Data will be collected from Q-IVF, MFR, Gynop and the Swedish National Pregnancy Register. We will use the unique Swedish identification number to identify the patients from the registers.
- P-Progesterone and reproductive outcome: Data will be collected in the same way as in the RCT.

SOURCE DATA AND CASE REPORT FORM

Patient medical records will serve as the source data and will be stored in accordance with Good Clinical Practice (GCP) guidelines. Data for this study will be captured using the Research Electronic Data Capture (RedCap) system, utilizing an electronic Case Report Form (eCRF). The information will be transcribed from paper source documents onto the eCRF by the site. To ensure accurate and reliable data collection, the study monitor will conduct verification and cross-check of the eCRFs against the investigator’s records (source document verification). The study database is located in Sweden at Clinical Trials Office (CTO), Center for Clinical Cancer Studies, Karolinska University Hospital.

DATA RECORDING AND RECORD KEEPING

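### The primary outcome definition stops counting at drop-out, which conflicts with the fixed three-year definition in the statistics section and, followed as written, scores women who leave before a birth as non-births

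*Protocol*

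**What the plan says.** Under Study Objectives, the definition of the primary outcome ends counting at "three years from first ART treatment or surgery or drop out from the study, whichever comes first". Under Statistical Considerations, the same endpoint is "defined as the proportion of participants achieving at least one live birth within three years following the initiation of treatment", with no mention of drop-out.

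The primary analysis compares the two proportions and reports a crude relative risk. The adjusted version is a log-binomial or modified Poisson model. Under the intention-to-treat rule, "participants are analyzed according to their randomized group regardless of adherence". The definition of the end of the trial adds: "Data from study participants that are lost to follow will be included in the final analysis".

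On missing outcomes, the Protocol states: "Missing outcome data will be handled under the missing-at-random assumption via maximum likelihood in mixed models". The clause that follows allows complete-case analysis, but for models that need complete covariates. On sample size, the calculation reaches 142 per arm and continues: "Allowing for 20% attrition, the planned total sample size is 350 participants".

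On data sources, Data Management and Quality Control takes the trial's data from medical records, with contact by phone or a secure platform if information is missing. The same section has "Obstetrical Outcomes: Either from medical records or the MFR at the end of the study". The Obstetrical Outcomes section also draws on the National Pregnancy Register, and the consented ten-year follow-up takes "live births from the Swedish Medical Birth Register (MFR) and The National Pregnancy Register". No register is named as a source for the primary outcome.

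**The concern.** The two definitions give different answers for the same woman. Suppose she leaves the study at 18 months without a birth and delivers at 30 months. Under Study Objectives her counting stopped at 18 months. Under Statistical Considerations she is a success.

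A time-to-event analysis could absorb the first definition by censoring her. The primary analysis has no censoring, so a woman who stays in the denominator without a counted birth is a non-birth.

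Both power and bias are at stake. Counting drop-outs as failures shrinks both proportions and the difference between them, whereas the attrition allowance appears to assume that drop-outs are removed and the rates stay undiluted. The trial is open label and compares two very different strategies, so drop-out need not be equal between arms. If it is not, the difference in drop-out enters the primary result directly.

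**Working it through.** **Inputs from the Protocol.** Rates of 55% (ART only) and 71% (surgery then ART), two-sided alpha 0.05, 80% power, 1:1 allocation, 142 per arm (284 total), 20% attrition and 350 planned. The separate figure of 323 in the same section is not used here.

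**Inputs that are assumptions.** The share g of drop-outs' births that occur before drop-out, and any split of drop-out by arm. The Protocol gives only the 20% total.

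**Step 1: reproduce the plan's figure.** With d = 0.16 and mean rate 0.63, the pooled-variance formula is

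n = [1.960·√(2·0.63·0.37) + 0.842·√(0.55·0.45 + 0.71·0.29)]² / 0.16² = [1.338 + 0.567]² / 0.0256 ≈ 141.8, so 142 per arm and 284 in total. This matches.

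**Step 2: what the attrition allowance implies.** 284/0.80 = 355 and 284 × 1.2 ≈ 341. The planned 350 lies between them and corresponds to removing 1 − 284/350 = 18.9%. Removing 20% of 350 leaves 140 per arm.

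**Step 3: power under each handling.** Power = Φ{[d√n − 1.960·√(2·p̄·(1−p̄))] / √(p₁(1−p₁) + p₂(1−p₂))}, where p̄ is the mean of the two rates. If 20% drop out of each arm, would have delivered at the arm's average rate, and are kept as non-births unless already delivered, the observed rate is p·(0.80 + 0.20·g). For g = 0 this gives 0.55 × 0.80 = 44.0% and 0.71 × 0.80 = 56.8%.

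| Handling of the 20% | ART | Surgery | n per arm | Power | Total N for 80% |
|---|---|---|---|---|---|
| Outcome obtained for all | 55.0% | 71.0% | 175 | 87.6% | 284 |
| Removed | 55.0% | 71.0% | 140 | 79.5% | – |
| Non-births, g = 0 | 44.0% | 56.8% | 175 | 66.9% | 478 |
| Non-births, g = 0.25 | 46.75% | 60.35% | 175 | 72.5% | 420 |
| Non-births, g = 0.50 | 49.5% | 63.9% | 175 | 77.8% | 370 |
| Non-births, g = 0.75 | 52.25% | 67.45% | 175 | 83.0% | 326 |

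With equal drop-out the relative risk stays at 0.568/0.440 = 1.29, so the cost is power.

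**Step 4: unequal drop-out (assumed splits, g = 0).**
- 15% ART, 25% surgery: 0.55 × 0.85 = 46.75% and 0.71 × 0.75 = 53.25%, so RR = 1.14 and power is about 23%.
- 25% ART, 15% surgery: 0.55 × 0.75 = 41.25% and 0.71 × 0.85 = 60.35%, so RR = 1.46.
- No true difference, both arms at 55%: the same two splits give RR = 0.88 and 1.13, each with about an 18% chance of a significant result in the false direction.

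**The case against.** The strongest reply is that the Protocol never says a woman who leaves is a failure. The Study Objectives clause may only mark when follow-up ends, the statistics section has the clean definition, and ending at drop-out is ordinary censoring in the secondary Kaplan–Meier and Cox analyses. Including lost women may mean using their data up to the point of loss. This stands to the extent that a reader who infers that failure scoring is settled goes further than the documents, because the fixed-window definition permits the other reading. The two definitions still have to be reconciled.

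A reader might also infer that the 80% power is lost. That holds only if few drop-outs' births come before they leave; at g = 0.75 power is 83%. Prognosis matters too. If drop-outs would have delivered at half the arm's rate, and none delivered before leaving, the observed rates are 0.55 − 0.20 × 0.275 = 49.5% and 0.71 − 0.20 × 0.355 = 63.9%, which gives 77.8%.

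A bias specifically against surgery might be inferred as well. The documents give no drop-out rate by arm, and the reverse split favours surgery.

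Ascertainment is also better than the clause suggests. Records and direct contact can recover a birth after a missed visit. Registers cannot recover everything, however: drop-out is not defined, women may withdraw consent, and the long-term register follow-up depends on consent.

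Finally, sensitivity analyses for missing data are promised, and imputation detail may sit in a statistical analysis plan that is not at hand. That detail is not the complaint. The complaint is that the rule the Protocol does state does not fit its primary analysis.

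**Conclusion.** The point holds as a conflict between two definitions of the primary outcome. One of them, combined with the stated analysis, counts a woman who leaves before a birth as a non-birth. A birth before drop-out still counts under either definition.

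If that definition is followed with 20% drop-out in each arm, power at 350 is 67% when none of the drop-outs' births precede leaving, and 72%, 78% and 83% at 25%, 50% and 75%. Removing drop-outs gives 79.5% and full ascertainment 88%. These figures rest on the planning rates and on drop-outs having their arm's average chance of a birth. That the plan meant to remove drop-outs is inferred from its arithmetic and is not stated in words.

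The bias under unequal drop-out (a relative risk of 1.14 or 1.46 in place of 1.29) rests on assumed splits of 15% and 25% and on no births before drop-out. It shows possible size in both directions and is not a forecast. The conflict should be fixed, and before outcome data are seen.

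**What to change.** - **Definition.** Delete the drop-out clause from the primary outcome definition and align it with Statistical Considerations: at least one live birth within three years of first treatment, regardless of drop-out from treatment or visits. Drop-out can remain a censoring time in the secondary time-to-event analyses.
- **Source.** Name the Medical Birth Register and the National Pregnancy Register, alongside medical records, as sources for the primary outcome in every randomised woman whose consent covers it.
- **Missing outcomes.** Treat as missing only women who withdraw consent for data use, refuse register use or emigrate. Replace the mixed-model rule for this endpoint with one suited to a binary outcome, for example multiple imputation within arm with best-case and worst-case bounds as sensitivity analyses.
- **Sample size.** Restate the attrition allowance to match, saying whether the 20% are removed, missing or ascertained.

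The cost is a protocol amendment, possibly new consent wording (the consent form is not at hand, so this cannot be judged here), and a final read-out that waits for register release. No additional women are needed: at the planning rates, 350 with full ascertainment exceeds the target power.

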# WHY THIS TRIAL IS NEEDED

BACKGROUND

Endometriosis

Endometriosis is a prevalent condition affecting 10% of female population of reproductive age, leading to pain and subfertility (1). An earlier systematic literature review and meta-analysis suggests that women with advanced endometriosis (revised American Society for Reproductive Medicine classification of endometriosis (rASRM) stage III-IV) have a lower likelihood of achieving clinical pregnancy/live birth compared to women without endometriosis, while this difference has not been observed for mild disease (stage I-II) (2).

Gynecological Ultrasound and staging

The prevalence of endometrioma and deep endometriosis found through systematic transvaginal ultrasound on women referred for ART treatment in Sweden has been estimated at 21.8% (3). Additionally, 75.8% of those with endometriosis were unaware of their condition prior to diagnosis (3). In recent years, two staging systems, namely the American Association of Gynecologic Laparoscopists (AAGL) Endometriosis classification (4, 5) and #ENZIAN (6) have gained prominence owing to their accuracy when juxtaposed with surgical findings.

Surgical Treatment

Women with endometriosis seem to experience pain relief after bowel surgery due to endometriosis (7, 8). Consensus from the European Society of Human Reproduction and Embryology (ESHRE) indicates that surgery can be performed prior to treatment with assisted reproductive technologies (ART) (7). Additionally, the number of spontaneous pregnancies is high after surgery on patients with deep endometriosis (10). Furthermore, in patients with endometriosis stage I-II or in infertile patients with endometriomas, surgery can in some cases be considered to improve fertility (7-9). However, the risk of severe complications in patients undergoing rectal surgery is up to 10% including anastomosis leakage and fistulas (10, 11).

Fertility treatment

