# STUDY OBJECTIVES

HYPOTHESIS

First line surgery (prior to ART treatment) in women with endometriosis AAGL stage III-IV will result in improved cumulative live birth rate (CLBR) as compared to first line ART.

PRIMARY OBJECTIVE

To assess whether surgery conducted prior to ART in women with endometriosis AAGL stage III-IV increases chances of CLBR as compared to first line ART.

.

SECONDARY OBJECTIVES

To evaluate whether surgery prior to ART treatments in women with endometriosis AAGL stage III-IV will result in improved cumulative pregnancy rate (CPR) and lower miscarriage rate as compared to first line ART.

To compare whether surgery prior to ART treatments in women with endometriosis AAGL stage III-IV will result in shorter time to live birth or pregnancy as compared to first line ART.

To investigate if surgery prior to ART treatments in women with endometriosis AAGL stage III-IV will result in better reproductive outcomes per IVF cycle and a lower rate of recurrent implantation failure (RIF).

To assess if surgery prior to ART treatments in women with endometriosis AAGL stage III-IV will result in lower rate of infections after oocyte pick-up requiring treatment with antibiotics as compared to first line ART?

To evaluate if surgery prior to ART treatments in women with endometriosis AAGL stage III-IV result in higher Quality of life and less pain measured with Endometriosis Health Profile (EHP-30) and Numeric Rating Scale (NRS) before ART, i) at the time of oocyte retrieval, ii) two months after ART and iii) at the three-year follow-up visit as compared to first line ART.

To explore whether surgery prior to ART treatments in women with endometriosis AAGL stage III-IV will be cost effective compared with first line ART?

To examine if surgery prior to ART treatments in women with endometriosis AAGL stage III-IV will result in reduced pregnancy and delivery complications, as well as fewer complications within 8 weeks postpartum, compared to first line ART.

To investigate whether serum progesterone level on the day of frozen embryotransfer in hormone replacement cycles in patients with severe endometriosis is associated with reproductive outcomes (LBR, pregnancy rate, miscarriage rate) and to determine if there is any difference in p-progesterone level between the two different study groups first line ART vs first line surgery in women with endometriosis AAGL stage III-IV?

PRIMARY OUTCOME MEASURE

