*Assisted reproductive technologies data (for each IVF/ICSI-cycle, max 3):*

- Complication – yes/no
- Type of complication (infection, ovarian hyperstimulation syndrome (OHSS), bleeding)
- Time from surgery to first oocyte pick-up
- Type of IVF protocols (GnRH agonist protocol/GnRH antagonist protocol)
- Total dose/mean daily dose of follicle stimulating hormone (rFSH) /human menopausal gonadotropin (hMG)
- Duration of IVF stimulation (days)
- Cancelled cycle (before or after oocyte pick up (OPU)) (excluding freeze all cycles)
- Reason of cancelled cycle
- Type of ovulation triggering [GnRH agonist (Gonapeptyl/Suprecur/Suprefact/Synarela) / Ovitrelle]
- Date of OPU
- Freeze all cycle (yes/no) and reason of that
- Number of retrieved oocytes (GV/MI/MII)
- Performed fertilisation method (ICSI/IVF)
- Sperm – fresh vs frozen
- Donor sperm – yes/no
- Origin of sperm – ejaculated/ epidydimal / testicular
- Oocytes – fresh vs frozen
- Number of inseminated oocytes
- Number of fertilised oocytes
- Number of good quality embryos defined according to Gardner criteria as AA, AB and BB for blastocysts (23) or top and good quality based on the number of blastomeres, the fragmentation rate and the multinucleation of blastomeres for cleavage stage embryos (24).
- Number of frozen blastocysts (D5 or D6)
- Date for fresh embryo transfer
- Embryo age at fresh embryo transfer (D2, D3, D4, D5 or D6)
- Number of embryos transferred (SET/DET)
- Type of embryo transfer (Fresh/Frozen)
- Type of protocols for Frozen-thawed ET (Natural Cycle (NC), HRT, Letrozol-stimulated, gonadotropinstimulated)
- Use of GnRH downregulation in Frozen-thawed HRT cycle (yes/no, number of days)
- Total estrogen dose and type of estrogen preparations in HRT FET-cycle
- Endometrial thickness prior to embryo transfer in HRT-FET
- Cycle day of endometrial thickness measurement in HRT-FET
- P progesterone level on the day of ET in HRT-FET
- Date of frozen ET
- Urinary pregnancy test (positive/negative)
- Gestational age at pregnancy ultrasound
- Fetal heartbeat at ultrasound (present/absent)
- Number of foetuses
- Number of gestational sacs
- Result foetus 1 (miscarriage, abortion, ectopic pregnancy, delivery)
- Date for delivery / end of pregnancy foetus 1
- Result foetus 2 (miscarriage, abortion, ectopic pregnancy, delivery)
- Date for delivery / end of pregnancy foetus 2
- Result foetus 3 (miscarriage, abortion, ectopic pregnancy, delivery)
- Date for delivery / end of pregnancy foetus 3

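### The miscarriage rate counts biochemical losses that are captured routinely only after embryo transfer, which may bias the per-pregnancy comparison in favour of surgery

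*Protocol*

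**What the plan says.** In the protocol, Study Objectives (Definition of secondary outcome measures), the miscarriage rate is given as a frequency and a proportion of "spontaneous loss of any clinical and biochemical pregnancy before week 22 and/or extrauterine pregnancy", "occurring between first treatment and end of follow-up". It covers any mode of conception. No denominator is named for the proportion. In the same section, the cumulative pregnancy rate counts "all pregnancies confirmed with ultrasound", and time to pregnancy also requires ultrasound.

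The secondary objective is directional: surgery should give "improved cumulative pregnancy rate (CPR) and lower miscarriage rate as compared to first line ART".

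Three other places determine which losses are seen:

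- **Covariates, Assisted reproductive technologies data.** The single pregnancy-test entry, "Urinary pregnancy test (positive/negative", stands in a list collected for each IVF/ICSI cycle.
- **Schedule of Events Table.** Between the two-month postoperative visit and the three-year contact, the only time points are the oocyte retrievals and two months after each.
- **Data Management, Data Collection.** Data come from medical records, and participants are contacted when information is missing.

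On spontaneous conception, the background (Surgical Treatment) says that "the number of spontaneous pregnancies is high after surgery on patients with deep endometriosis". The section on the surgical procedure also associates cyst enucleation with better chances of spontaneous conception. ART is delayed by two to three months after surgery, and that interval lies inside the counting window.

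**The concern.** After an embryo transfer a test result is recorded, so a biochemical loss is seen as a matter of routine. After a spontaneous conception, a biochemical loss is seen only if the woman happens to test and the result reaches her record. An early loss that nobody reported also leaves no visible gap that would prompt a call.

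If spontaneous conceptions make up a larger share of conceptions in the surgery arm, as the protocol expects, a larger share of that arm's biochemical losses goes unrecorded. The proportion of recorded pregnancies that are lost then falls in the surgery arm for a reason unrelated to pregnancy outcome. The shift is toward the protocol's own hypothesis, on an outcome named in the objectives of a trial whose findings are to enter national guidelines (Significance of Study).

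**Working it through.** The protocol gives no figure for the miscarriage rate, so there is none to reproduce. The check is an expected-value model in which the true risk of loss is the same in both arms. Every input is an assumption, because the documents give none of them.

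| Input | Meaning | Assumed value |
|---|---|---|
| b | biochemical loss per conception | 10% to 30% |
| c | clinical loss among conceptions that pass the biochemical stage | 15% |
| d | share of biochemical losses detected after spontaneous conception (100% after transfer) | 0 to 80% |
| s | spontaneous share of conceptions | 10% to 50% surgery, 5% ART |

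**Formula.** Recorded losses per conception are b + (1−b)c after transfer and bd + (1−b)c after spontaneous conception. Recorded pregnancies per conception are 1 and bd + (1−b) respectively. Hence

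rate = [(1−s)(b + (1−b)c) + s(bd + (1−b)c)] / [(1−s) + s(bd + 1−b)]

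**Middle case** (b = 20%, c = 15%, d = 30%):

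- Surgery, s = 30%: (0.7×0.32 + 0.3×0.18) / (0.7 + 0.3×0.86) = 0.278 / 0.958 = 29.0%
- ART, s = 5%: (0.95×0.32 + 0.05×0.18) / (0.95 + 0.05×0.86) = 0.313 / 0.993 = 31.5%
- Spurious relative risk: 0.290 / 0.315 = 0.92

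**Range** (c = 15%, ART spontaneous share 5%):

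| b | d | s, surgery | Surgery | ART | RR |
|---|---|---|---|---|---|
| 10% | 80% | 10% | 23.3% | 23.4% | 0.997 |
| 10% | 50% | 15% | 22.9% | 23.3% | 0.98 |
| 20% | 30% | 30% | 29.0% | 31.5% | 0.92 |
| 20% | 0 | 50% | 24.4% | 31.3% | 0.78 |
| 30% | 0 | 50% | 30.0% | 39.6% | 0.76 |

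The spurious difference runs from 0.1 to 9.6 percentage points. It is exactly zero if d = 100% or if the spontaneous shares are equal. Otherwise it favours whichever arm has the larger spontaneous share. At the pessimistic end (d = 0, an assumed 110 pregnancies per arm), the chance of a falsely significant result in favour of surgery is about 9% (b = 20%, s = 30%) to 32% (b = 30%, s = 50%), against a nominal 2.5%.

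**Per woman instead of per pregnancy.** In the middle case with equal numbers of conceptions, the ratio is 0.278 / 0.313 = 0.89. If the surgery arm has 20% more conceptions, it is 0.888 × 1.2 = 1.07. The sign changes once the surgery arm has about 13% more conceptions (0.313 / 0.278 = 1.13).

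**After the change.** Clinical losses per ultrasound-confirmed pregnancy are (1−b)c / (1−b) = c in both arms, whatever b, d and s are. This assumes that every pregnancy past the biochemical stage is scanned before it is lost.

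**The case against.** The strongest points on the other side are these.

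- **Testing confined to ART is an inference.** The protocol never says so. The variable list is not a full account of outcome collection: it has no field for spontaneous pregnancy, which is a named outcome, and the case report form is not shown. This stands as a limit on certainty. Home tests and follow-up calls would shrink the bias, though they would not reverse it in the per-pregnancy proportion.
- **The ultrasound items stand in the same ART list.** By the same reasoning, scans of spontaneous pregnancies might not be collected either. In part this stands. But the cumulative pregnancy rate already requires ultrasound confirmation for every conception, so the protocol has committed itself to that information. It has made no such commitment for biochemical losses.
- **The direction depends on the denominator.** This stands. None is named, and a per-woman rate can move against surgery.
- **The gap in spontaneous conception may be small.** The delay of ART is short, hormonal treatment between surgery and ART is foreseen, and women needing donor sperm or with male-factor infertility are eligible. Spontaneous pregnancies can also occur in the ART arm. This stands, and it is why the range reaches almost to 1.
- **ART-only rates are already planned.** Miscarriage per embryo transfer and per cycle are listed, so a comparison with uniform testing will sit beside the overall rate. That softens the problem but leaves the overall rate, which serves the stated objective, as it is.

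A reader might infer that spontaneous conceptions as such escape detection, or that the definition will make surgery look better even with no effect. The documents support neither. Only biochemical losses of spontaneous conceptions are at risk of being missed; spontaneous pregnancies that reach ultrasound are counted. The outcome of the comparison depends on the unnamed denominator and on quantities the protocol does not give. Pooling extrauterine pregnancies is not an error either: results are coded separately, so splitting them out is mainly a reporting preference.

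**Conclusion.** The point holds in a limited form. Followed as written, the plan is likely to give arm-dependent capture of biochemical losses, and this may bias the per-pregnancy miscarriage proportion toward the hypothesis of "lower miscarriage rate as compared to first line ART". The argument rests on two things: capture outside ART is less complete than after transfer (inferred from the data list and schedule), and spontaneous conceptions form a larger share in the surgery arm (stated as an expectation, without a number).

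The size is not derivable from the documents. Under the assumed inputs the spurious relative risk lies between 0.76 and 0.997, and mild assumptions give about 0.98. Under Statistical Considerations the secondary endpoints are supportive and exploratory, and the primary cumulative live birth rate is unaffected. The definition should be changed, but it does not threaten the trial's main conclusion.

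**What to change.** For the between-arm comparison, define miscarriage as loss before week 22 among ultrasound-confirmed pregnancies, the unit the cumulative pregnancy rate already uses, and name those pregnancies as the denominator. Report biochemical loss per embryo transfer only, beside the miscarriage rate per transfer that the protocol already lists. State in the same definition whether extrauterine pregnancies belong to the rate.

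This is a rewording of one outcome definition. It needs no visit or test beyond what the cumulative pregnancy rate requires, provided ultrasound confirmation of spontaneous pregnancies is recorded. The cost is fewer counted events and slightly less precision. It removes most, but not all, of the differential detection: no scan is scheduled for spontaneous conceptions, so losses before a first scan may still differ somewhat by mode of conception. Keeping biochemical losses in the comparison would instead require equal pregnancy testing and reporting for all conceptions in both arms, which is a larger change.
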